#### Missing data handling

Missing data for the trait outcomes (BSCS, SSBS), analyses will be managed via pairwise availability with sensitivity checks using last-observation-carried-forward for descriptive ranges. For the state-levelEMA data, missing days will simply be omitted because Tau-U inherently tolerates unequal phase lengths and missing data points within time-series sequences. To rigorously assess the effect of intervention dosage, per-participant compliance (percentage of EMA prompts answered) will be reported and descriptive contrasts comparing high- compliance (≥ 60%) versus low- compliance (< 60%) will be conducted.

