### Model definition

The model is conceptualized as a developmental delivery architecture wherein human counselors establish the relational frame and developmental arc, while AI system executes the high-frequency micro-dosage required for proximal skill enactment. Critically, this intervention does not conceptualize AI as a counselor analog, therapist substitute, or diagnostic component, but as a systemic dosage amplifier. Counselors maintain primary responsibility for relational containment, while the AI autonomously delivers the high-volume, micro–developmental practice opportunities that human counselors cannot feasibly scale. This approach is grounded in the developmental reality that self-regulation and social connectedness are not cultivated through episodic learning, but through continuous, real-world repetition. The architecture therefore mirrors the mechanisms of motor-skill acquisition: micro-practice → consolidation → transfer. This counselor–AI co-delivery framework makes this repetition feasible within standard school constraints.

The intervention is deployed throughout eight consecutive school weeks. Each week focuses on one thematic developmental objective (see Table 1) and offers a synchronous 10–15-min counselor mini-session. This mini session serves as a vital “anchor point,” grounding the week’s developmental target in a supportive relational context while allowing the counselor to check ecological fit, safety, and progress. The remainder of the weekly dosage is delivered digitally through daily MI-style micro-nudges (e.g., ≤ 40 words). The sequence is intentionally graded to build capacity over time: initial weeks emphasize foundational awareness and micro-choice recognition; intermediate weeks prioritize active skill application in real-life contexts; final weeks focus on value mapping, identity congruence, and future transfer. In essence, the intervention is paced not by superficial “topic rotation,” but through the cumulative scaffolding of practice complexity.

**Table 1 tab1:** Structured eight-week progression of developmental objectives and measurable indicators.

Week	Theme	Weekly skill focus	Measurable outcome wording	Measurement schedule
0				Weeks −2 to −1: Consent, demographics, BSCS/SSBS (pre), two-week daily EMA baseline (Phase A)
1	Awareness	Noticing internal states & situational triggers	Student(s) can label at least one emotional state + one situational trigger per day	

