2	Micro-Choices	Identifying ‘choice points’ in daily routines	Student(s) can describe one moment/day where a micro-choice was made intentionally	
3	Regulation Moves	Using micro-regulation strategies in real time	Student(s) can report using at least one regulation move during a difficult moment	
4	Social Signals	Reading emotional/social cues in peers	Student(s) can identify one social cue observed in a peer interaction per day	Weeks 1–8: Daily EMA, weekly mini-session, fidelity log
5	Connection Behaviors	Performing pro-social action steps	Student(s) can report one specific pro-social action per day	
6	Real-World Practice	Applying skills in naturalistic school contexts	Student(s) can name one applied skill used in a school scenario that occurred	
7	Integration & Identity	Linking skills to values and identity	Student(s) can articulate one personal value and how a behavior reflected it	Week 8: BSCS/SSBS (post)
8	Transfer & Future Self	Projecting skills into future-oriented plans	Student(s) can describe one future scenario where learned skills will be used	

The AI augmentation is delivered through two channels. Channel 1 deploys daily micro-nudges aligned with the overarching weekly objective; these function as single-turn reflective invitations that increase the density of developmental prompts across the student’s daily ecological environment. Channel 2 consists of short-form (3–5 turn) micro-coaching dialogues, triggered either by voluntarily user initiation or automatically triggered following a 24-h lapse in engagement. Both channels are strictly reflective, offering no directive advice, clinical instruction, or evaluative feedback. The goal is to systematically increase the frequency with which the student monitors internal states, detects micro-choice moments, decodes social signals, and reflects on prosocial behaviors. Over the 8 weeks, this dual-channel architecture aims to expose the student to dozens of micro self-regulation enactments and relational affordances that incrementally accumulate to drive sustained and measurable developmental change.

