## Method

### Setting and participants

The intervention is designed for implementationwithin mainstream high school counseling settings serving adolescents aged 14–18. This ecological frame is intentional. As a feasibility study, the sample size is determined by the need to evaluate implementation applicability and estimation precision rather than statistical power for clinical efficacy. A target sample of 40–60 students from routine school caseloads, is sufficient to yield narrow confidence intervals (CIs) for recruitment/retention/compliance and to visualize heterogeneous individual-level micro-trajectories within an authentic delivery context. Feasibility will be evaluated against four pre-specified operational thresholds: (a) a recruitment rate ≥ 70% of eligible students; (b) a retention rate of ≥ 80% (defined as completing both pre- and post-intervention trait measures); (c) a median EMA compliance of ≥ 60% for daily prompts (1–7 Likert scale) across Weeks 1–8; (d) an intervention fidelity of ≥ 75% (defined as weeks where all three checklist items are met). These thresholds were derived from established benchmarks in the feasibility and pilot trial literature (Billingham et al., 2013; Eldridge et al., 2016). The 70% recruitment and 80% retention rates are widely adopted as minimum indicators of a viable study pipeline for a subsequent full-scale trial. The 60% EMA compliance threshold reflects the empirically observed lower bound of acceptable ecological momentary data completeness in adolescent digital health studies (Shiffman et al., 2008); compliance below this level produces phase lengths insufficient for reliable Tau-U estimation. The 75% fidelity threshold is grounded in the intervention science literature’s recommendation that at least three-quarters of protocol sessions be delivered as specified before efficacy conclusions can be considered (Bellg et al., 2004). Together, these benchmarks ensure that a positive feasibility verdict is substantively meaningful rather than nominally so.

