### Measures

Trait-level self-regulation will be assessed using the Brief Self-Control Scale (BSCS; Tangney et al., 2004), a short 13-item self-report instrument, psychometrically validated across 11 languages, and widely used as a robust proxy for dispositional self-regulatory capacity in adolescent and adult populations. Items are scored on a 5-point Likert scale ranging from 1 (*not at all like me*) to 5 (*very much like me*). The BSCS captures stable individual differences in the ability to modulate attention, emotion, impulses, and behavior, making it appropriate for detecting trait-level shifts in response to developmental scaffolding. A sample item is, “I wish I had more self-discipline.” The BSCS has demonstrated good internal consistency, (*α* = 0.83; Tangney et al., 2004). In a feasibility design, the objective is not to optimize latent factor modeling, but to index whether directional improvement is present at the level of standardized mean difference. Consequently, the BSCS will be administered one week prior to intervention onset and immediately post-intervention.

Trait-level social connectedness will be indexed using the Simple School Belonging Scale (SSBS; Whiting et al., 2017), a 10-item instrument that quantifies the subjective perception of being psychologically included, relationally valued, and socially embedded within the school’s peer ecology. A sample item is, “I feel like my ideas count at [school name].” School belonging is one of the most tightly coupled environmental predictors of both academic persistence and socioemotional well-being in adolescence. The SSBS functions as a proximal phenotype of this social connection, and changes in SSBS scores provide a trait-level marker of whether the intervention’s repeated micro-affordances generalized into durable, perceived relational embeddedness. The SSBS has also demonstrated strong internal consistency (*α* = 0.96; Whiting et al., 2017).

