### Data analysis strategy

The analytical framework of this study is structured to evaluate three outcomes: (a) trait-level directional movement, (b) state-level micro-trajectory change, and (c) mechanism enactment evidence. These three analytical layers correspond directly to the theoretical dimensions the intervention engages in disposition, enactment, and meaning-in-use. To assess trait-level shifts, pre- and post-intervention changes in the BSCS and SSBS will be quantified using a within-subject standardized mean difference, following Lakens’s (2013) generalized within-subject effect size formulation. This approach mitigates dependence on between-subject variability and is appropriate for feasibility designs wherein each participant serves as their own baseline control (Lakens, 2013, 2017). To robustly index the magnitude of directional movement, 95% confidence intervals will be calculated, despite traditional null-hypothesis significance testing not being required under feasibility logic.

State-level EMA sequences (Phase A baseline vs. Phase B intervention) will be analyzed using Tau-U with baseline trend correction. Importantly, correcting for baseline trend prevents inflated effect-size estimates that might otherwise be misattributed to intervention exposure rather than pre-existing directional drift. Tau-U allows non-overlap evaluation even with small samples and is currently the most methodologically defensible effect-size metric for SCED micro-regulation sequences. Qualitative data will be evaluated via reflexive thematic analysis, though explicitly restricted to mechanism verification rather than narrative phenomenology. Coding will be deductive and anchored to the weekly objective architecture.

Finally, to integrate the three evidence streams, a triangulation matrix will be constructed to map (a) trait-level shifts, (b) state-level effect estimates, and (c) qualitative mechanism evidence. The purpose of this synthesis is not to blend subjective narrative with statistical data, but to evaluate whether the targeted mechanism signal is reliably detectable across heterogeneous measurement modes. Methodological convergence across these domains confirms intervention feasibility, while signal divergence indicates a structural implementation malfunction.

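### With only a pre and a post trait score, the planned LOCF check fixes the change of students without a post score at zero, so it does not show how informative dropout could alter the trait result.

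*Protocol article*

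**What the plan says.** The schedule in Table 1 (Protocol article, Model definition) places the trait scales at two occasions: "Weeks −2 to −1: Consent, demographics, BSCS/SSBS (pre), two-week daily EMA baseline (Phase A" and "Week 8: BSCS/SSBS (post". No trait measurement is listed in between. The Measures section agrees for the self-control scale: "the BSCS will be administered one week prior to intervention onset and immediately post-intervention".

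Under Data analysis strategy, trait change is "quantified using a within-subject standardized mean difference", and "95% confidence intervals will be calculated"; significance testing is not required.

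Under Missing data handling, trait outcomes are analysed on available pairs, with "sensitivity checks using last-observation-carried-forward for descriptive ranges". No other sensitivity check for missing trait data is named.

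Under Setting and participants, the planned size is given as "A target sample of 40–60 students". Retention counts as adequate when at least 80% complete both trait measurements.

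**The concern.** A sensitivity check on missing outcomes should show how far the result could move if those who left differ from those who stayed. With two occasions, LOCF cannot do this. The only earlier value is the baseline, so the imputed change is zero whatever happened to the student. The output is set by two numbers already known, the retained share and the completers' mean.

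The Measures section says the trait scales are there to indicate whether change goes in the hoped-for direction. A check that cannot change the sign of that mean cannot challenge that reading. Trait shifts are also one of the three evidence streams in the triangulation matrix, and the article offers its design as a template for later randomised trials, so the rule may be copied.

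**Working it through.** The article gives no effect size, SD of change or interval width for the trait outcomes, so there is no stated figure to reproduce. The inputs are as follows.

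- From the article: N = 40 to 60; retention threshold 80%; one pre and one post trait score.
- Assumed: completers' mean change m = 0.30 in units of their SD of change s (s = 1); share without a post score q = 0.20, that is, retention exactly at the threshold; every such student has a baseline.

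**Students affected.** 0.20 × 40 = 8 and 0.20 × 60 = 12.

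**LOCF mean.** Imputed post = pre, so imputed change = 0, and

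mean(LOCF) = (1 − q) × m + q × 0 = 0.80 × 0.30 = 0.24.

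For any q below 1 this has the same sign as m and lies between 0 and m.

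**What the overall change could be.** If dropouts changed on average by δ, the overall mean is 0.80 × 0.30 + 0.20 × δ:

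| δ (SD of change) | overall mean |
|---|---|
| −0.50 | 0.14 |
| −0.25 | 0.19 |
| 0 (LOCF) | 0.24 |
| +0.25 | 0.29 |
| +0.50 | 0.34 |

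The complete-pair result and the LOCF result span 0.24 to 0.30. Both ends of the table lie outside that span. The overall mean reaches zero at δ = −(0.80 × 0.30)/0.20 = −1.2. For completer means of 0.2 and 0.5 the tipping points are −0.8 and −2.0. LOCF reports none of this.

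**Interval width, if an interval is computed on LOCF data.** The variance of change with the zeros added is about (1 − q)s² + q(1 − q)m² = 0.80 + 0.16 × 0.09 = 0.814, SD 0.902. Relative to the completers,

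(SE LOCF / SE completers)² = (1 − q)² × (1 + q × (m/s)²) = 0.64 × 1.018 = 0.652, ratio 0.81.

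With t quantiles and sample variances the 95% half-widths are:

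| N | completers | LOCF | ratio |
|---|---|---|---|
| 40 | 0.361 (n = 32) | 0.288 | 0.80 |
| 60 | 0.290 (n = 48) | 0.233 | 0.80 |

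For standardised changes from 0 to 0.8 the ratio is 0.79 to 0.84 at 80% retention, about 0.90 to 0.93 at 90%, and 0.69 to 0.76 at 70%. The narrowing disappears only above a standardised change of about 1.53, 1.68 or 1.86 for 10%, 20% or 30% dropout.

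**Check on the standardised measure.** The plan reports a standardised difference, whose denominator also shifts when dropouts' baselines enter. A simulation of 4,000 replicates per setting assumed a true change of 0.3 SD, pre–post correlation 0.5 or 0.7, N of 40 or 60 and 20% dropout completely at random. The mean standardised change fell from about 0.31 in completers to 0.24 under LOCF. Coverage of the true change by the 95% interval fell from about 95% to 90–92%.

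**The case against.** The strongest reply is that LOCF is not empty. It shows the case of no change in dropouts and pulls an improving estimate toward zero, which is the less favourable side for a single-arm study looking for improvement. That stands, but it is a single point, and worsening among dropouts would lie beyond it.

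A reader might infer that the plan will publish a falsely narrow confidence interval. The article does not support that. It confines LOCF to descriptive ranges and specifies the 95% interval in another section, for the trait effect size, with missing scores handled by available pairs. The narrowing is conditional on a step the article does not state, although an SD computed on the LOCF changes would be compressed by the same zeros.

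A reader might also take one fifth as the most that can be missing. The 80% figure is a feasibility threshold, not a cap. And a student without a baseline has nothing to carry forward, so the zero applies only to those with a baseline and no post score.

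Finally, the consequence is limited. None of the four operational thresholds uses trait change, no significance test is required, and the Limitations section disclaims causal and efficacy claims. This bears on how much the point matters, not on whether the check works.

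**Conclusion.** The point holds in a narrow form. That LOCF assigns zero change follows from the article's own two-occasion schedule and needs no assumption. That the LOCF mean is retention times the completers' mean is exact for the raw mean when all non-completers have a baseline, and approximate for the standardised difference. The sizes (0.24 against 0.14 to 0.34, and about 20% narrowing if an interval is computed) rest on the assumed completer change, dropout share and dropout changes.

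The main complete-pair analysis is unaffected, and nothing here overturns a feasibility verdict. The defect is that the only sensitivity check named for missing trait data does not do the job of one. It is a cheap improvement rather than a fundamental flaw.

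**What to change.** In Missing data handling, replace LOCF for the BSCS and SSBS with a delta-adjusted or tipping-point table for students who have a baseline but no post score. Assume mean changes of, for example, −0.5, −0.25, 0, +0.25 and +0.5 SD for them, and report the overall change under each beside the complete-pair estimate and its 95% interval. Using both signs keeps the range from being one-sided; the zero row retains what LOCF shows. State how many students each row applies to.

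Optionally, add multiple imputation with a few predictors, such as the baseline score and a summary of the available EMA ratings. With about 32 to 48 completers a large imputation model is not realistic, and students missing the post score may also lack late EMA data.

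The cost is about one sentence of text, a little more analysis and a wider reported range. No new data are needed.

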In this intervention, the counselor supervises fidelity, not content generation. The synchronous weekly mini session(s) serves to anchor and facilitate relational connection, provide developmental interpretation, and maintain clinical boundaries. To support this, counselors receive an auto-generated weekly summary of the student’s (a) micro-nudge delivery and engagement, (b) micro-coaching activity, and (c) reflective note submissions. The counselor’s task is not to manually “grade” or “correct” but to contextualize the AI-facilitated micro-work within the student’s authentic relational ecology, and to intervene if emotional distress or dysregulation emerges. Ultimately, this design upholds the core ethical framework that the AI augments the intervention dosage, but human counselors remain fundamental anchors of the developmental and relational process.

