Momentary (state-level) regulations will be assessed through a daily, single-item Ecological Momentary Assessment (EMA) self-rating prompt delivered throughout the eight-week intervention phase. Adolescents are prompted with the question: “Right now, how effectively are you managing your emotions and behavior?” and respond on a 1–7 Likert scale (1 = *not effectively at all*, 7 = *very effectively*). Basically, this item is designed to capture real-time regulatory enactment rather than a retrospective or global self-assessment. Thus, EMA state trajectories recorded across Phase B provide a mechanism-level time-series dataset optimally structured for single-case Tau-U analysis.

All outcome indicators depend on student self-report, the protocol also incorporates two additional informant-based measures. Teacher behavioral ratings will be collected at pre- and post-intervention timepoints using a brief four-item adaptation of the Social Skills Improvement System (SSIS; Elliott et al., 2008) targeting observable classroom regulation behaviors (e.g., “This student recovers quickly from frustration”) and prosocial conduct (e.g., “This student initiates positive interactions with peers”). Items are rated on a 4-point frequency scale (1 = never, 4 = almost always) by the student’s primary classroom teacher. Parent or guardian reports will be collected using a parallel four-item brief form targeting home-context regulation and social behavior, administered via a secure online survey link at the same two timepoints. These informant sources provide convergent evidence from ecologically distinct observational contexts, reducing the sole reliance on student self-report and mitigating single-source inflation of perceived effects.

Implementation of fidelity will be captured via weekly counselor fidelity summaries. To minimize administrative burden and avoid interpretive drift, this documentation uses a structured, three-item binary checklist. The counselor simply records whether: (1) micro-nudges were opened at least four times during the week; (2) the student submitted at least one reflective note; and (3) the student concretely described at least one pro-social or regulation-aligned behavior. Counselors may optionally add a single-sentence contextual remark if relevant. These logs do not serve as qualitative data for phenomenology, but rather as direct fidelity evidence confirming that the designed mechanism was actively enacted.

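### The dosage contrast sorts students by the share of EMA ratings answered, which measures outcome completeness and not the intervention received

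*Protocol article*

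**What the plan says.** Missing data handling, in the protocol article, gives both the purpose and the measure: "To rigorously assess the effect of intervention dosage, per-participant compliance (percentage of EMA prompts answered) will be reported". It then adds that "descriptive contrasts comparing high- compliance (≥ 60%) versus low- compliance (< 60%) will be conducted". It does not name the outcome to be contrasted, or say whether the percentage covers the baseline weeks as well as Weeks 1–8.

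The same article describes the two quantities separately.

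- **EMA.** Under Measures: "Momentary (state-level) regulations will be assessed through a daily, single-item Ecological Momentary Assessment (EMA) self-rating prompt". It is the state-level outcome. Table 1 also schedules it before the intervention starts, as a "two-week daily EMA baseline (Phase A".
- **Dosage.** Model definition starts from the weekly counselor mini-session and continues: "The remainder of the weekly dosage is delivered digitally through daily MI-style micro-nudges". A second channel is added: "Channel 2 consists of short-form (3–5 turn) micro-coaching dialogues". EMA is not listed as a component.
- **Records of exposure.** Model definition says counselors receive a weekly per-student summary of "micro-nudge delivery and engagement, (b) micro-coaching activity, and (c) reflective note submissions".

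**The concern.** A measure of whether students answered the outcome question stands in for how much intervention they received. The two can diverge in either direction, and the planned comparison would not show it. EMA response also fixes how many Phase B points enter each student's Tau-U, so the high and low groups differ by construction in the completeness and precision of the state outcome.

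At stake is the interpretation of one descriptive comparison. The article presents the AI component as a way of amplifying dosage, and under Practical contribution it offers its dosage logic and measurement scheme for later trials to adopt. A difference between the two EMA groups could be read as a dose-response signal, and a lack of difference as its absence. Neither reading would be justified.

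**Working it through.** The plan states no figure that depends on this point, so there is none to reproduce. The check sets the definitions side by side, then illustrates the possible size.

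**1. Is EMA response a dose by the document's own terms?**

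| Item | Place | Role given |
|---|---|---|
| EMA prompt | Measures | Single-item daily outcome rating |
| EMA in Weeks −2 and −1 | Table 1; Research design | Baseline, before any intervention |
| 60% EMA compliance | Setting and participants | Feasibility criterion, justified by the phase length Tau-U needs |
| Nudges, dialogues, mini-sessions | Model definition | The intervention delivered |
| Nudge engagement, coaching activity, notes | Model definition (weekly summary) | Per-student uptake |
| Prompts opened, notes submitted | AI system specification (weekly logs) | Uptake counts |
| At least four nudge opens a week | Measures; Appendix B | Fidelity item |

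The dosage contrast uses the first and third rows and none of the last four. No section gives an exposure-based reason for 60%.

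**2. What the 60% cut counts.** The number of prompts per week is not stated; assume 5 (school days) or 7.

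- Phase B prompts: 8 × 5 = 40, or 8 × 7 = 56.
- The cut: 0.60 × 40 = 24 ratings, or 0.60 × 56 = 33.6, so 34 ratings.
- Student X answers all 40 (or 56) ratings and opens no nudge: 100%, high dose.
- Student Y opens every nudge and answers 20 of 40 (or 28 of 56) ratings: 50%, low dose.
- If the percentage also covered Phase A, which the text leaves open, 10 of 50 or 14 of 70 prompts (20%) would fall where the dose is zero.

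**3. How many students could be misplaced.** Let ρ be the correlation between EMA response and true exposure. The document does not give it. Assume the two are bivariate normal and each is split at its median. The share of students in the wrong dose group is then arccos(ρ)/π. A dose contrast that is linear in exposure shrinks by about the factor ρ.

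| ρ | Wrong group | Of 40 students | Of 60 students | Contrast multiplied by |
|---|---|---|---|---|
| 0 | 50% | 20 | 30 | 0 |
| 0.3 | 40% | 16 | 24 | 0.3 |
| 0.5 | 33% | 13 | 20 | 0.5 |
| 0.7 | 25% | 10 | 15 | 0.7 |
| 0.9 | 14% | 6 | 9 | 0.9 |

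The student counts multiply the unrounded share by the target sample of 40 and 60, before attrition; for example 0.403 × 40 ≈ 16 and 0.253 × 60 ≈ 15. A 60% cut is a median split only if median compliance is exactly 60%, which is the feasibility criterion just met. With higher compliance the groups become unequal and these shares are only a guide.

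**The case against.** The best defence is that little hangs on this contrast. It is descriptive, the article disclaims causal efficacy, significance testing is not required, and none of the four feasibility thresholds uses it. Uptake also appears elsewhere, in the fidelity checklist, so EMA response is not the study's only indicator of engagement. All of that stands, and it limits the severity. It does not repair the mislabelling, because the fidelity items are not linked to the dosage contrast. EMA response may track engagement, and answering a self-rating might itself prompt self-monitoring, but the article presents EMA only as measurement.

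A reader might also infer several stronger points that the document does not support.

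- *All of the true dose is already logged.* Nudge opens, notes and overall coaching activity are recorded weekly. No section shows mini-session attendance being recorded, or whether a dialogue was started by the student or by a lapse.
- *The lapse rule gives disengaged students more dose.* Dialogues can be "automatically triggered following a 24-h lapse in engagement", but a lapse is not defined as unanswered EMA prompts, and being sent a dialogue is not the same as taking part in it.
- *The contrast simply compares students on the outcome, with confounding by baseline self-regulation added in full.* Answering daily prompts may well reflect self-regulation. The trait outcomes, however, are within-student changes, so stable differences in level largely cancel. Baseline could still predict change, but by an amount nobody can derive from this document.
- *The result will be used as dose-response evidence in the later trial.* It could be read that way; nothing says that it will be.
- *The analysis contradicts the Limitations.* The word for an effect sits badly with the statement there that changes cannot be attributed to the intervention. That is loose wording, not a conflicting analysis.

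**Conclusion.** The point holds as a mislabelled measure. Followed as written, the plan assesses dosage with a variable that the document itself defines as outcome measurement, cut at a level it justifies by data completeness. The comparison would describe survey response and completeness, not exposure.

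The extent of misclassification cannot be fixed from the document. Under the bivariate normal, median-split assumption it runs from about 40% of students at a correlation of 0.3 to about 25% at 0.7, and it would be small only if EMA response followed exposure very closely. The harm is confined to the interpretation of a descriptive contrast in a single-arm feasibility study. It is worth correcting because suitable exposure records for the AI channels are already described and the change is small.

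**What to change.** 1. Under Missing data handling, remove the dosage wording from the EMA sentence. Keep per-student EMA compliance and the split at 60% as a data-completeness check, and state which weeks the percentage covers.
2. If a dosage description is wanted, base it on the weekly exposure records: the share of delivered nudges that were opened, and micro-coaching activity. Add mini-session attendance only if it is recorded.
3. Call the result an association and say that it remains subject to self-selection, since students choose whether to open nudges just as they choose whether to answer ratings. A descriptive contrast is enough; the defect does not call for a regression model.

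The cost is a change of wording and a slight extra descriptive analysis. One practical point needs confirming: Research design says that export functions are disabled, so the study team should make sure that the weekly counts can reach the analysis file. If they cannot, step 1 alone removes the error.
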